### Tongue strength and range of motion

Brief, non-invasive testing will measure tongue function, including strength and range of motion, using published methods. A video recording of L-ROM and strength will be assessed using published, validated methods. The IOPI digital manometer will measure maximum isometric lingual strength to assess the maximum pressures generated by the tongue (inter-operator reliability of 0.75) [28,29].

### Clinician graded lymphedema and fibrosis

Clinician-graded soft tissue palpation sores in the bilateral submental, anterior, and lateral neck will be recorded using the Head and Neck External Lymphedema and Fibrosis (HN-LEF), which has a reported inter-operator reliability of 0.91 [30,31]. This tool uses ordinal scoring to evaluate the type (A-D) and severity grade (1–5) of soft tissue changes.

### Data management and ethics

The data collected for this study are part of a larger cohort effort to collect comprehensive outcomes data from consenting patients in the Oropharynx program at the MD Anderson Cancer Center in Houston, Texas (MDA-OPC). The collection is approved under MD Anderson IRB #PA14–0947 for MD Anderson Oropharynx Cohort patients who consent to tongue testing procedures (optional procedure #2 on the parent consent form). Patients scheduled for appointments in the Head and Neck Center will be identified by either an attending physician or an appropriately trained designee. During clinic appointments, potential subjects will be informed of their eligibility and asked if they would be interested in participating in research. In the privacy of the exam room, physicians or designees with appropriate training will discuss all aspects of the study with potential subjects and answer any questions. Subjects will be given a copy of the Informed Consent and further instructed about the study and the elements of the consent document. The subject will be given as much time as needed to review and discuss the study and consent, and the research nurse, research data coordinator, attending physician, or designee will answer any remaining questions. Non-English-speaking patients will consent to use an MD Anderson Translator and a verbal translation preparatory sheet, in accordance with MD Anderson policies for Informed Consent translation, in that patient’s primary language. Patients may withdraw from the study at any time without any penalty. The MD Anderson Institutional Review Board classifies this study as minimal risk and does not monitor this study for adverse events. The PI is responsible for monitoring adverse events. Risk will be evaluated by the electromyographer upon review of the patient’s medical history and medication.

Since 2015, 1,750 OPC patients have enrolled with detailed, interdisciplinary characterization of exposures, diagnostic/staging, treatment, disease control, and longitudinal collection of validated clinician- and patient-reported survivorship outcomes from diagnosis through 5-year survival. All longitudinal MDA-OPC clinical data is securely stored in REDCap® and DMI, an institutionally secured Data Management Services platform. Our DMI-based MDA-OPC database contains 14 data forms, 1182 imported variables, 439 manually entered variables, and 18 customized reports, with nightly updates from integrated data sources. Anyone interested in analyzing the collected data can submit a request to the database oversight committee ([contact]). Functional outcomes, PROs, and electrodiagnostic data will be de-identified and provided to the [name] Research Lab for analysis under MD Anderson IRB #PA14–0947. Code and models will be stored in a public GitHub repository within the group “[name]/hdsemg_pipeline.” Because the software is not complete, the source code will be made publicly available when the analysis is complete.

### Outcomes definition

#### Primary objective.

For analysis of the primary objective, the primary endpoint will be _HDS_EMG classification of XII neuropathy (yes/no, then graded) in relation to the gold-standard needle EMG classification. We expect to show that features such as frequency of interference patterns and tongue fasciculations correlate between _HDS_EMG and needle EMG, demonstrating that _HDS_EMG is a feasible, rapid, non-invasive biomarker for tongue neuropathy. We will consider _HDS_EMG feasible for this exploratory analysis if more than 80% of the signal recordings meet the quality criteria. We also expect that a neural network with a multiclass activation function will grade tongue neuropathy progression on a continuous scale.

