**Objective:**

In an exploratory study, examine the feasibility of _HDS_EMG for rapid, non-invasive screening of hypoglossal nerve (CN XII) function and estimate the prevalence of hypoglossal neuropathy before and after oropharyngeal radiotherapy, and associate with patient-reported and clinician-graded functional outcomes. Machine learning performance will be measured through sensitivity, specificity, and F1 score, with a target area under the curve > 0.7 based on literature-reported EMG sensitivity and specificity.

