### Objectives

#### Primary objective: Examine the feasibility of _HDS_EMG for rapid, non-invasive screening of XII nerve function.

We plan to show that a machine learning algorithm trained on features of _HDS_EMG waveforms collected during a brief series of tongue tasks will detect CN XII neuropathy and grade its severity on a continuous, more sensitive scale than existing EMG. Time-frequency features extracted from _HDS_EMG will be used to detect tongue neuropathy grade using linear discriminant analysis, ensemble machine learning classifiers, and a neural network with a multiclass activation function, providing insight into the relationship between _HDS_EMG and tongue function degradation. Tongue _HDS_EMG will also be decomposed into estimates of constituent MU spike trains for analysis with a convolutional neural network.

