### Evaluation criteria

The performance of machine learning classifiers will be divided into two classification settings: binary (CN XII neuropathy vs. no confirmed CN XII neuropathy) and multiclass (neuropathy grade). In binary classifiers, we aim for AUC ≥ 0.70 to support _HDS_EMG as an inexpensive, non-invasive quantitative metric for screening OPC survivors for CN XII neuropathy. Narayanaswami et al. report that electromyographers with 10–20 years of experience have a diagnostic sensitivity of 0.77 and a specificity of 0.71 for neuropathy. [24] This will serve as our benchmark for reliable performance for all binary model development. For the 10% validation set, we will measure model performance simply by the percentage of correctly diagnosed cases of neuropathy. As a secondary validation outcome, we will compare the _HDS_EMG neuropathy severity grade with the gold-standard needle EMG grades.

Multiclass classification will use micro- and macro-F1 scores to evaluate the validity of a refined CN XII neuropathy grade prediction. Saliency mapping for the CNN will reveal which signal regions contribute to each neuropathy grade prediction. Machine learning models will be evaluated using SHapley Additive exPlanations (SHAP) to investigate which features contribute to the model predictions [39].

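### The only sentence that decides whether HDsEMG is feasible looks at signal quality alone and cannot respond to the primary endpoint, and the plan does not say how it combines with the AUC target

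*Protocol article*

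**What the plan says.** - **Objective** (Objectives, primary objective): "Examine the feasibility of _HDS_EMG for rapid, non-invasive screening of XII nerve function".
- **Primary endpoint** (Outcomes definition, Primary objective): "the primary endpoint will be _HDS_EMG classification of XII neuropathy (yes/no, then graded) in relation to the gold-standard needle EMG classification".
- **Feasibility rule** (same paragraph): "We will consider _HDS_EMG feasible for this exploratory analysis if more than 80% of the signal recordings meet the quality criteria". No other sentence in the article is worded as a decision on feasibility.
- **Expectation about features** (same paragraph, just before the rule): features are expected to "correlate between _HDS_EMG and needle EMG, demonstrating that _HDS_EMG is a feasible, rapid, non-invasive biomarker for tongue neuropathy". No threshold is attached.
- **Accuracy target**: the Abstract's Objective has machine learning performance "with a target area under the curve > 0.7 based on literature-reported EMG sensitivity and specificity". Evaluation criteria says "In binary classifiers, we aim for AUC ≥ 0.70 to support _HDS_EMG as an inexpensive, non-invasive quantitative metric for screening OPC survivors", and takes as benchmark that experienced electromyographers "have a diagnostic sensitivity of 0.77 and a specificity of 0.71 for neuropathy".
- **Quality criteria** (Data analysis and machine learning plan, and the text under Fig 1): they use the rolling mean absolute value of each channel. Rest recordings are never rejected. Protrusion and isometric channels can be.
- **Classifier failure** (Discussion): if classification does not adequately detect neuropathy, electrical impedance myography is named as the alternative biomarker.

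**The concern.** The endpoint and the decision rule measure different things. The endpoint asks whether HDsEMG agrees with needle EMG. The rule asks whether enough signals were usable. Both stand under one objective, whose wording is about screening, and both bear on the word feasible.

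With good recordings and a classifier that carries no information, the decision sentence returns feasible while the primary endpoint shows that neuropathy is not detected. The report could then state either conclusion, and the protocol would not settle which. A later reader who sees feasibility confirmed under a screening objective would take it as evidence about detection.

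**Working it through.** **1. Does the rule depend on the endpoint?** Its inputs are the effort curve of each protrusion and isometric channel, and automatic acceptance at rest. The needle EMG label does not enter. The probability of meeting the rule is therefore the same for every value of the AUC.

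**2. How demanding is 80%?** The cut-off has no derivation to reproduce. Table 1 does reproduce: 2 × (30 + 30 + 10) = 140 s. It lists 6 recordings per session, of which 2 are at rest.

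- Recording as unit: required pass rate in the tasks that can fail = (0.80 − 2/6) / (1 − 2/6) = 0.70.
- Seconds as unit: (0.80 − 60/140) / (1 − 60/140) = 0.65.
- Counts, with 36 patients and one six-recording session each: 36 × 6 = 216 recordings. More than 80% means at least 173. Rest supplies 72 automatically, leaving 101 of 144 (70.1%).

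The rule speaks of recordings while the rejection criteria act on channels, so these figures assume the stated unit.

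**3. How often is the rule met?** Binomial P(X ≥ 101 of 144), treating recordings as independent for illustration:

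| True pass rate, protrusion and isometric | P(rule met), any AUC |
|---|---|
| 0.65 | 0.11 |
| 0.70 | 0.53 |
| 0.75 | 0.92 |
| 0.80 | 0.998 |

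**4. How often would a chance classifier reach AUC 0.70?** Expected positives, from the protocol's own rates: 12 × 0.05 + 24 × 0.42 = 10.7 of 36. From the exact null (Mann–Whitney) distribution of the AUC, one score per patient:

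| Patients on whom the AUC is judged | P(AUC ≥ 0.70 given true AUC 0.50) |
|---|---|
| All 36 (11 vs 25; 10 vs 26) | 0.029; 0.034 |
| About 7, development set (3 vs 4; 2 vs 5) | 0.20; 0.29 |
| 3 to 4, validation set (1 vs 3; 1 vs 2 or 2 vs 2) | 0.25; 0.33 |

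The set sizes follow from the patient-wise 70/20/10 split: 25.2, 7.2 and 3.6 patients.

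**5. How often would the two criteria disagree?** Multiply the probabilities, taking the criteria as independent.

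- Chance classifier, all 36 patients, pass rate 0.75 in the tasks that can fail: 0.92 × 0.97 = 0.89 feasible with a missed AUC. At pass rate 0.70: 0.53 × 0.97 = 0.51. At 0.65: 0.11 × 0.97 = 0.11.
- Chance classifier judged on 3 to 7 held-out patients, pass rate 0.75: 0.92 × (0.67 to 0.80) = 0.62 to 0.74.
- Uniform pass rate over all 216 recordings, ignoring automatic acceptance at rest: P(X ≥ 173) = 0.98 at 0.85, 0.53 at 0.80 and 0.05 at 0.75. The first gives 0.98 × 0.97 = 0.95.
- Disagreement can run the other way. With uniform acceptance 0.75 and a classifier of true AUC 0.80 (binormal, 11 vs 25), AUC ≥ 0.70 is reached with probability about 0.89, and 0.95 × 0.89 = 0.85 of such studies would miss the quality rule and meet the AUC target.

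**6. How precise is an AUC of 0.70 on 36 patients?** Hanley–McNeil with 11 vs 25: A/(2 − A) = 0.538 and 2A²/(1 + A) = 0.576. Variance = [0.21 + 10 × (0.538 − 0.49) + 24 × (0.576 − 0.49)] / 275 = 0.0101, so SE = 0.10. The 95% interval is about 0.50 to 0.90.

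**The case against.** The best defence is that the rule is about recordability and was never meant to settle detection. It is limited to this exploratory analysis. Support for screening use is tied elsewhere to the AUC target, which also stands in the Abstract's Objective. The Discussion treats inadequate classification as a failure and turns to another biomarker. Nowhere does the article say that passing the 80% rule alone meets the primary objective. A reader might infer that, but the text does not support it.

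A reader might also count feature correlation as a third, equal route to success. It is only an expectation, without a threshold.

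The study is a single-site pilot of 36 patients, the authors claim only exploratory interpretation, and no confirmatory decision depends on the word.

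Much of this stands, and it limits the point. What remains is that the rule sits under the primary objective without being labelled technical, the accuracy target is phrased as an aim, and no sentence connects them. Exploratory status excuses low precision. It does not excuse a pre-stated rule that leaves out the primary endpoint.

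**Conclusion.** The point holds as an unreconciled pair of criteria. The only feasibility decision is blind to the primary endpoint, so feasible could be declared with an uninformative classifier. The rule is also easier to meet than 80% suggests: just over 70% of the protrusion and isometric recordings, if the recording is the unit.

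The documents do not fix how often the criteria would conflict. A reader might infer that they would disagree in about 95% of studies, always in favour of feasible. That is one scenario (85% uniform acceptance, true AUC 0.50, AUC judged on all 36 patients). Over the chance-classifier scenarios shown, the probability of a feasible verdict with a missed AUC target runs from about 0.05 (0.05 × 0.97, uniform acceptance 0.75) to 0.95, and the conflict can run in the opposite direction.

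All these probabilities assume independent recordings, one session of six per patient and the listed class splits. Recordings from one patient will be correlated, the tasks are repeated with HDsEMG alone, and several time points are possible. The finding that the rule ignores accuracy needs none of these assumptions.

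This should be corrected, but it does not invalidate the study.

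**What to change.** In Outcomes definition, Primary objective:

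1. State that more than 80% acceptable recordings supports only the conclusion that recording is technically feasible. Name the unit (recording or channel), and compute the percentage on protrusion and isometric tasks, or report it by task.
2. Allow the conclusion that HDsEMG is feasible for screening hypoglossal nerve function only if the AUC criterion in Evaluation criteria is also met on the primary endpoint. Because both criteria must be met, no multiplicity adjustment is needed.
3. Judge that AUC on out-of-sample, patient-level predictions pooled across patient-wise cross-validation folds, not on the 3 to 4 validation patients, and report its confidence interval. Name in advance the model to which the criterion applies, and keep feature selection and tuning inside the training folds.
4. Use one form of the target: it is strictly greater than 0.7 in the Abstract and at least 0.70 in Evaluation criteria.
5. Label the feature correlations as supportive.

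The cost is a stricter condition for the headline conclusion and slightly more analysis work, since scores from different folds must be on a comparable scale before pooling. No new data are needed.

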#### Secondary objective.

For analysis of the secondary objective, the primary endpoint of XII neuropathy will be grade>0, classification of denervation potentials per needle EMG. Secondary endpoints of tongue function will include the total L-ROM score and MILS in the anterior and posterior tongue.

### Data analysis and machine learning plan

Clinical measures will be used to confirm the diagnosis and grade of neuropathy. We expect a pilot sample size of 36 patients with needle EMG and _HDS_EMG to provide ample statistical power to develop a machine-learning classification algorithm, since acquiring 2 minutes and 20 seconds of EMG data at 10 kHz will yield 50.4 million values (36 pts x 140 sec x 10 kHz). For 32-channel _HDS_EMG at 4 kHz (the threshold for the SAGA device), that is 645.12 million values (36 patients x 140 sec x 4 kHz x 32 EMG simultaneous channels). Still, we acknowledge our limitations in determining the optimal sample sizes, as we do not yet have _HDS_EMG data in OPC patients. If the initial analysis shows insufficient performance, we will assess EMG and _HDS_EMG subsets to further increase the training and test dataset sizes. Fig 1 depicts the general data processing pipeline that will translate _HDS_EMG measures into CN XII neuropathy grade. Signals will be preprocessed using MATLAB R2023a software (MathWorks; Natick, MA). Experimental _HDS_EMG will be denoised using a bandpass filter from 20–500 Hz. The signal quality assessment for each task consists of the following. First, a rolling mean absolute value of each channel (window size 400 samples) will represent the apparent effort exerted by the patient.

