All accepted signals are divided into 2-second segments for feature extraction. The Discrete Wavelet Transform (DWT) will be used to extract time series features (waveform length, zero crossings, slope signal changes, root mean square, autoregressive coefficient, mean absolute value, and integrated mean absolute value) and time-frequency features (mean instantaneous frequency, mean first derivative, amplitude-modulated bandwidth, frequency-modulated bandwidth, and spectral moment of power spectral density) [32]. We will perform Mann—Whitney U-tests with α = 0.05 to determine whether these features are relevant to neuropathy through the following comparisons: reduced recruitment vs. no reduced recruitment; polyphasia vs. no polyphasia; increased amplitude vs. no increased amplitude; and increased duration vs. no increased duration. To further demonstrate the clinical relevance of _HDS_EMG features, we will use Pearson’s Correlation Coefficients and multiple regression analysis to express correlations between _HDS_EMG features and tongue functional outcomes (L-ROM and IPOI pressure).

The full dataset will be partitioned patient-wise into 70% for training, 20% for development, and 10% for validation. Features from the training set that discriminate neuropathy severity will be selected using linear discriminant analysis. Missing data may occur during time-frequency feature extraction, as some calculations can trigger divide-by-zero errors, especially for low-frequency components. If this occurs, such examples will be rejected as artifacts. If any class label is represented by less than 10% of the data, recording-wise mean imputation will be performed to augment the number of unique examples in the underrepresented classes.

We intend to train an initial decision tree and support vector machine (SVM), followed by ensemble methods using both trees and SVMs, where possible: Random Forest Classifier, Gradient Boost, and Bagging. We will also train a neural network classifier with a softmax activation function for multiclass classification. Hyperparameter optimization will be performed using 5-fold cross-validation and verified using the development set. To account for potential class imbalance, all ensembled learning methods will be trained using class-weighted sampling to ensure that individual classifiers within the ensemble see class-balanced subsets of the data. Machine learning will be performed using SciKit Learn [33].

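### The ample-power claim for the classifier rests on counts of digitised values, but the information is limited by 36 patients and gives about 47% power at the protocol's own AUC target, at best

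*Protocol article*

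**What the plan says.** All of this is in the protocol article.

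- **Size of the classifier study** (Data analysis and machine learning plan): 36 patients are expected "to provide ample statistical power to develop a machine-learning classification algorithm, since acquiring 2 minutes and 20 seconds of EMG data" yields millions of values. The reason given is a count of values: "EMG data at 10 kHz will yield 50.4 million values (36 pts x 140 sec x 10 kHz") for needle EMG, and "645.12 million values (36 patients x 140 sec x 4 kHz x 32 EMG simultaneous channels") for the surface recordings. No effect size, alpha or power value is given for the classifier.
- **Caveat** (same section): "Still, we acknowledge our limitations in determining the optimal sample sizes, as we do not yet have _HDS_EMG data in OPC patients".
- **Fallback** (same section): if initial performance is insufficient, "we will assess EMG and _HDS_EMG subsets to further increase the training and test dataset sizes".
- **Feature tests** (same section, after Fig 1): "All accepted signals are divided into 2-second segments for feature extraction". Mann-Whitney tests at alpha 0.05 are then planned "to determine whether these features are relevant to neuropathy through the following comparisons": reduced recruitment, polyphasia, increased amplitude and increased duration. The unit of these tests is not stated.
- **Data split** (same section): by patient, 70% training, 20% development, 10% validation.
- **Target** (Evaluation criteria): AUC of at least 0.70 for the binary classifier. The validation set is judged by percentage correct.
- **Secondary objective** (same section as the size statement): 12 patients in each of three timing groups, a maximum CI half-width of 0.29, and 80% power at alpha 0.10 for 5% pre-RT against 42% post-RT.

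**The concern.** The argument runs from the number of digitised values to statistical power. Values recorded milliseconds apart, on neighbouring electrodes of one tongue, all relate to the same patient's nerve. What the classifier must learn and be tested on is the relation between signal and diagnosis, and the diagnosis varies between patients. Sampling at 8 kHz instead of 4 kHz would double 645.12 million to 1,290.24 million values without adding a patient.

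The claim supports the primary endpoint, surface-EMG classification against needle EMG. The Discussion says the resulting sensitivity and specificity will inform later sample sizes, so precision overstated here would carry forward. The fallback repeats the reasoning: subsets of the same recordings make the test set look larger without adding patients, and the step is taken because a result disappointed. If the feature tests also treat segments as independent, their nominal 5% would not hold.

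**Working it through.** **1. The protocol's own figures.**

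- Needle EMG: 36 × 140 × 10,000 = 50,400,000. Reproduces.
- Surface EMG: 36 × 140 × 4,000 × 32 = 645,120,000. Reproduces.
- Secondary objective: two-proportion power for 12 versus 24 patients, 5% versus 42%, two-sided alpha 0.10, is 81.0%. The largest exact half-width for n = 12 is 0.289. Both agree with the text and both count patients.

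The fault is therefore in what the first two numbers are used for, not in the multiplication.

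**2. Patients by diagnosis.** From the rates in the secondary-objective power statement: 0.05 × 12 + 0.42 × 24 = 0.60 + 10.08 = 10.68, so about 11 positive and 25 negative.

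**3. Best-case precision at AUC 0.70.** Hanley-McNeil, with A = 0.70:

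- Q₁ = A/(2 − A) = 0.5385; Q₂ = 2A²/(1 + A) = 0.5765; A² = 0.49.
- SE² = [A(1 − A) + (n₁ − 1)(Q₁ − A²) + (n₀ − 1)(Q₂ − A²)]/(n₁n₀)
- = [0.21 + 10 × 0.0485 + 24 × 0.0865]/275 = 2.77/275, so SE = 0.100.
- 95% CI: 0.70 ± 1.96 × 0.100 = 0.50 to 0.90.

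Power against 0.50 (two-sided 0.05): the null SE is √(37/(12 × 275)) = 0.106, so power = Φ[(0.20 − 1.96 × 0.106)/0.100] ≈ 47%. With an 18/18 split it would be 54%. At a true AUC of 0.80 with 11/25 it would be 85%. For 80% power at AUC 0.70, about 77 patients are needed at 30% prevalence, or 63 at 50%.

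This assumes that all 36 patients supply out-of-sample predictions.

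**4. Precision under the stated split.** 36 × 0.70, 0.20 and 0.10 give 25.2, 7.2 and 3.6 patients.

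- Development set: 7 × 11/36 ≈ 2 positive, 5 negative. SE² = [0.21 + 1 × 0.0485 + 4 × 0.0865]/10 = 0.0604, so SE ≈ 0.25.
- Validation set: 3 of 4 correct has an exact 95% CI of 19% to 99%. The chance that it holds no neuropathy case at all is 21% with 4 patients and 32% with 3.

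**5. What more segments add.** 140 s / 2 s = 70 segments per channel per patient, or 2,520 per channel over 36 patients. The effective number is 2,520/(1 + 69 × ICC). The ICC is not in the documents; the range is assumed.

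| ICC (assumed) | Effective observations |
|---|---|
| 0.05 | 566 |
| 0.2 | 170 |
| 0.5 | 71 |
| 0.8 | 45 |

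Pooling all 32 channels (2,240 segment-channels per patient) at ICC 0.5 gives 72 instead of 71.

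**6. Feature tests, only if segments are pooled.** A null simulation (1,500 runs per setting, 11 versus 25 patients, 70 segments each, nominal 5%) gave these rejection rates:

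| ICC (assumed) | Pooled segments | Patient means |
|---|---|---|
| 0.05 | 34% | 6% |
| 0.2 | 60% | 5% |
| 0.5 | 73% | 5% |

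A separate simulation of the same setting gave 35% at ICC 0.05 and 74% at 0.5.

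**The case against.** The study is labelled pilot and exploratory, admits that its sample size could not be optimised, and allows only exploratory interpretation in the Discussion. The split is by patient, so segments should not leak between sets. The feasibility criterion (more than 80% of recordings of adequate quality) does not depend on power. AUC 0.70 is a target, and no test against 0.50 is planned. These points stand and lower the severity, but they do not rescue the inference. The caveat concerns missing prior data, not dependence within patients, and the claim of ample power remains beside it.

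Several stronger readings go beyond the documents:

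- *Power is absent.* It depends on the true AUC, and 85% at 0.80 is respectable. What can be said is that power is not shown.
- *The whole sample size is unjustified.* The secondary objective has sound patient-based figures.
- *The Mann-Whitney tests are invalid.* The article does not state their unit, and a full analysis plan may fix it. The simulated 11 versus 25 split is neuropathy yes or no, not the four planned comparisons, whose group sizes are not given. The 70 segments pool all tasks and both sides before any channel is rejected. The rates are illustrative. Classifier features are chosen by discriminant analysis on training data, so the text does not carry false positives from these tests into the primary endpoint.
- *Each patient has one grading.* Both tongue sides are examined, and the text does not say whether grades are per side. Even so, there would be at most 72 sides, clustered in 36 patients.
- *Results will be re-cut until they pass.* One loosely described step is planned, not a repeated search.

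**Conclusion.** The point holds in this limited form and should be fixed. It is an error of statistical reasoning: the value counts are right but do not support ample power for the classifier. With the patient as the unit, the best case at AUC 0.70 is a CI of about 0.50 to 0.90 and about 47% power against 0.50. Under the stated split, precision is far worse. These figures rest on the protocol's expected neuropathy rates, one diagnosis per patient and the Hanley-McNeil approximation, which is crude for 2 versus 5 patients. The subset fallback adds no independent patients. The concern about the feature tests is conditional on segments being pooled, and its size depends on an assumed ICC.

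**What to change.** 1. Delete the value counts as an argument for power. State patient-level precision for AUC, sensitivity and specificity under the evaluation scheme actually used, and say which patients the AUC is computed on. Quote 0.50 to 0.90 only as a best case under patient-level cross-validated predictions from all 36; under the 70/20/10 split it would overstate precision.
2. Remove the step that enlarges the training and test sets with subsets when performance is insufficient. Alternatively, confine it to training patients, label it post hoc, and keep the patient as the unit for any test-set precision.
3. State the unit of the Mann-Whitney and correlation analyses. Use one summary per patient, or a cluster-aware method such as a mixed model or patient-level permutation.

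The cost is a few sentences and at most one aggregation step in the analysis code. No patients or procedures are added. The stated precision becomes less favourable.

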### Needle electromyography and nerve conduction

Intramuscular EMG will assess insertional activity in the genioglossus muscle, innervated by CN XII, as a marker of denervation [23]. Needle EMG is reported to have an inter-operator reliability of 0.53 [24]. EMG recordings will be conducted by a cancer neurologist fellowship trained in clinical neurophysiology and denervation potentials graded per standard neurologist’s grading:

0 - None

1 - Persistent, single train of potentials in at least two areas

2 - Moderate number of potentials in three or more areas

3 - Many potentials in all areas

4 - Full interference patterns of potentials

EMG and NCS may also be performed in the trapezius muscle (innvervated by CN XI), as the region is easily accessible for non-invasive testing and represents a muscle within the irradiated field with lower cranial nerve innervation. Both quantitative and qualitative EMG may be assessed [25]. Needle EMG will not be conducted if platelets are < 50,000. The intramuscular EMG will require a clinical visit with the neurologist.

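### The fallback after poor performance enlarges the test set from the same 36 patients and, read literally, could admit needle-EMG recordings as scored examples

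*Protocol article*

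**What the plan says.** The fallback stands in the Data analysis and machine learning plan section: "If the initial analysis shows insufficient performance, we will assess EMG and _HDS_EMG subsets to further increase the training and test dataset sizes".

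The same section shows what plain EMG means there. It opens with "We expect a pilot sample size of 36 patients with needle EMG and _HDS_EMG to provide ample statistical power" to develop a classification algorithm, and gives as the reason that "acquiring 2 minutes and 20 seconds of EMG data at 10 kHz will yield 50.4 million values". The 4 kHz, 32-channel HDsEMG volume is counted separately. The 10 kHz signal is therefore the needle recording, and its values are counted towards developing the classifier.

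Needle EMG is also the reference standard. Under Outcomes definition, Primary objective, "the primary endpoint will be _HDS_EMG classification of XII neuropathy (yes/no, then graded) in relation to the gold-standard needle EMG classification". The Needle electromyography and nerve conduction section says how the grade arises: "EMG recordings will be conducted by a cancer neurologist fellowship trained in clinical neurophysiology and denervation potentials graded per standard neurologist’s grading".

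Elsewhere the classifier input is HDsEMG alone. This is so in the primary objective under Objectives, in the Fig 1 caption, and in the description of the pipeline that follows the fallback sentence. Evaluation criteria sets an AUC of at least 0.70 for binary classifiers as the mark that supports HDsEMG for screening.

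**The concern.** There are two separate problems.

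1. **What may enter the test set.** If needle segments are scored there as inputs, the reference modality is partly being tested against a grade read from that same modality. The resulting AUC mixes two signals and does not answer the primary question, which is how well HDsEMG reproduces the needle classification.

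2. **When and how the test set changes.** The trigger is a disappointing result, and the response alters the data on which performance is judged. Subsets of recordings from the same 36 patients add correlated examples, not patients. This holds whatever role needle EMG plays.

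At stake is the meaning of the 0.70 criterion. The Discussion also says the work will provide benchmark sensitivity and specificity for later sample-size estimates, so a distorted figure could carry forward.

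**Working it through.** **The plan's own figures.**
- Needle: 36 × 140 s × 10,000 Hz = 50.4 million values.
- HDsEMG: 36 × 140 s × 4,000 Hz × 32 = 645.12 million values.

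Both reproduce exactly.

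**Possible needle share, w, if the two signals were pooled.** The protocol cuts signals into 2-second segments: 140 / 2 = 70 per patient, 36 × 70 = 2,520 in all, before any quality rejection.
- Each HDsEMG channel is one example: 2,520 / (2,520 + 2,520 × 32) = 1/33 = 3.0%.
- Share of raw values: 50.4 / (50.4 + 645.12) = 7.2%.
- Each 32-channel segment is one example: 2,520 / (2,520 + 2,520) = 50%.

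These shares use the protocol's own count of one 140-second set per patient. The text under Table 1 also has the tasks repeated with HDsEMG alone. If that second set entered too, the 50% would fall to 1 / (1 + 2) = 33%.

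**Effect on the AUC.** If scores share one scale, with a common distribution among patients without neuropathy, then

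pooled AUC = (1 − w) × AUC(HDsEMG) + w × AUC(needle).

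The document gives no AUC for either signal. Assume HDsEMG at 0.50 or 0.55, and needle at 0.90 or 0.95 respectively. The gap is 0.40 in both cases, so the pooled AUC is the HDsEMG AUC plus 0.40 × w.

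| Needle share w | Added | From 0.50 | From 0.55 |
|---|---|---|---|
| 3.0% | 0.012 | 0.51 | 0.56 |
| 7.2% | 0.029 | 0.53 | 0.58 |
| 33% | 0.133 | 0.63 | 0.68 |
| 50% | 0.200 | 0.70 | 0.75 |

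The share needed to reach 0.70 is (0.70 − 0.50) / 0.40 = 50% from 0.50, and (0.70 − 0.55) / 0.40 = 37.5% from 0.55.

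**Independent patients.** The patient-wise split gives 36 × 0.70 = 25.2 for training, 36 × 0.20 = 7.2 for development and 36 × 0.10 = 3.6 for validation. Further subsets of these recordings leave all three counts unchanged.

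**The case against.** The fallback sentence does not say that needle segments become classifier inputs. It says subsets will be assessed, and that term is undefined. Needle and surface signals are recorded simultaneously, so it could mean cutting the paired recordings into more windows, with needle EMG on the label side only. Every description of the model input names HDsEMG, and no processing route is given for a needle signal as input. Needle data used in training alone would leave an HDsEMG-only test valid. All of this stands, and it makes the first problem conditional.

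The benign reading is still not the easiest one. The 50.4 million needle values are offered as a reason for adequate power to build the classifier, whereas a label contributes grades, not values. Segmentation into 2-second pieces is already part of the main analysis.

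A reader might infer that needle segments would predict their own label. The documents do not support that. The High-density surface electromyography section has the electromyographer evaluate the needle signal before the simultaneous recording, and the grade depends on activity across several areas. A short needle segment is the same modality, but not plainly the signal that was graded.

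It is also fair that a large distortion needs a large needle share. Signal-quality rejection works channel by channel, which fits the 3% case. The assumed needle AUC is generous beside the protocol's own reader figures (sensitivity 0.77, specificity 0.71). The Discussion plans for HDsEMG failing and limits itself to exploratory conclusions.

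None of this answers the second problem: the test set changes after a poor result under every reading.

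**Conclusion.** The point holds in conditional form. As written, the fallback permits needle-EMG recordings in the test set, contrary to the HDsEMG-only input stated elsewhere. If they were scored there, the re-run AUC could not be taken as HDsEMG performance against needle EMG. Under the assumed AUCs the distortion runs from negligible (about 0.01 at a 3% share) to decisive (0.20 at 50%), and the plan does not fix the share.

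A reader might go further and conclude that the re-run would certainly stop measuring HDsEMG, or that a failed classifier would be reported as a success. The documents support neither. They leave the role of needle data in the fallback open, and nothing says a mixed-signal result would be presented as HDsEMG screening performance.

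What does not depend on the reading is that a performance-triggered change to the test set adds no independent patients and can bias the reported result. That bias cannot be sized from the documents. The exploratory label lowers the stakes but does not remove the problem, because this is a stated rule and not a detail left to a fuller document.

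**What to change.** Amend the fallback sentence and add a short rule:

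- In every development and validation (test) set, including any re-run, HDsEMG is the only classifier input and needle EMG supplies only the label.
- Remove the test set from the fallback. Any enlargement applies to training examples only, and the held-out patients and their recordings stay as first partitioned. Say what a subset is.
- Report the initial result beside any re-run.
- Report any model that uses the needle signal separately and label it as such.

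The essential part is the restriction on the evaluation sets, since needle data confined to training would not by itself invalidate an HDsEMG-only test. The cost is wording, and a fallback that yields fewer added examples.
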